## Discussion

AP is one of the most common diseases of the gastrointestinal tract, leading to serious emotional, physical, and financial human burden [19]. Patients with AP typically present with sudden epigastric or left upper quadrant pain. Severe abdominal pain is the hallmark symptom of AP, and sometimes radiates to the back, chest, or flanks [3]. Interestingly, the severity of pain may correlate with the severity of AP [20]. Therefore, aggressive control of pain can help to improve the quality of life and reduce the severity of pancreatitis in patients with AP, regardless of etiology. An effective treatment of pain in AP ranges from the administration of simple analgesic drugs, such as non-steroidal anti-inflammatory drugs, up to the administrations of potent opioid drugs according to the severity [4, 21]. However, the adequate treatment of pain is much more complex in clinical circumstances. While the World Health Organization (WHO) regimen is usually applied to the pain management [15], some interventional strategies should be considered in patients with severe AP-related complications. One reason for the challenge behind pain management is the high complexity of AP itself. Patients with necrotizing AP often suffer from severe pain attacks, associated pleural effusion , ascites, and even multiple organ failure. Despite the importance of controlling abdominal pain, most guidelines do not provide precise guidelines for abdominal pain relief [1–3].

Until the 1990s, opioid analgesics were used only for the treatment of moderate to severe acute pain and cancer pain, but recently, there has been an increase in long-term use for non-cancer pain such as in pancreatitis. Theoretically, because there is no ceiling effect in the use of opioid analgesics, they can be an attractive choice for the pain without improvement by non-analgesic agents [22, 23]. However, 80% of patients using opioid analgesics experience at least one side effect. The most common side effect is constipation. Vomiting, sedation, and drowsiness are also relatively common, and respiratory failure can occur if the initial dose is excessive or increases rapidly. In addition, long-term use may also cause serious side effects such as hyperalgesia, neuroendocrine dysfunction, and immunosuppression. Above all, the continued use of opioid analgesics can cause patients to become more physically and psychologically addicted to the drug over time [24]. Therefore, there is an urgent need to develop safe and effective methods to replace the use of opioid analgesics in the management of pain in patients with AP.

Acupuncture is already proven to be effective for a variety of pain types including abdominal pain [10], and there is no concern about dependency, so it can be a good alternative to opioid analgesics for the treatment of pancreatitis pain. This trial started from this idea at first, and was planned primarily based upon the previous study on patients with colorectal cancer surgery [13]. The study suggested that EA can reduce postoperative pain as well as the duration of postoperative ileus. The mean VAS of EA group on day 3 was 2.1 ± 1.2, which was significantly lower than that of sham group (3.2 ± 1.8, *P* < 0.001). Another previous study also has shown that EA could reduce the postoperative analgesic requirement and associated side effects in patients with abdominal surgery [25]. The analgesic effect induced by EA might be mediated by κ-opioid receptors through the release of dynorphin [26].

In this study, we aimed to demonstrate the hypothesis that EA would be more effective in pain control than SOC therapy in patients with AP. We set two different treatment groups, local and distal EA, to compare the effects according to acupoints. The two acupoints (CV12, CV13) in the local EA group are located in the abdomen, which might affect abdominal pain due to the location. Therefore, we have introduced the other arm, the distal EA group, which includes distal acupoints located in the arms and legs. The treatment in the distal EA group is expected to mask the location effect in the abdomen. Furthermore, the comparison between the two EA groups will provide valuable information on the effect of distal acupuncture in patients with abdominal pain. To the best of our knowledge, this trial is the first randomized controlled study to introduce EA, which is the representative method of oriental medicine, in the treatment of AP. Therefore, irrespective of the result, this study should give a critical result on the effect of EA. If the efficacy of EA is proven to be significant, changes in guidelines for the management of AP are expected in the future (Additional file 1).

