**Methods:**

This study is a randomized, controlled, three-arm, parallel-group, multi-center trial. Patients diagnosed with acute pancreatitis are enrolled and randomly assigned to EA 1, EA 2, or a control group in a 1:1:1 ratio. All the enrolled patients basically receive the conventional standard-of-care therapy for acute pancreatitis. Local EA is given in group EA 1, while local with additional distal EA is given in group EA 2. Local EA includes two acupoints, *Zhong Wan* (CV12) and *Shang Wan* (CV13), located in the abdomen, while distal EA includes 12 peripheral acupoints, *Zhong Wan* (CV12), *Shang Wan* (CV13), *He Gu* (LI4), *Nei Guan* (PC6), *San Yin Jiao* (SP6), *Xuan Zhong* (GB39), *Zu San Li* (ST36), and *Shang Ju Xu* (ST37). The patients randomized to the EA 1 and EA 2 groups undergo one session of EA daily from day 1 until day 4, or until pain resolves. The primary endpoint is the Visual Analog Scale (VAS) change for pain on day 5. Secondary endpoints include daily VAS, requirement of analgesics, changes of inflammatory markers, time to pain disappearance, and hospital days.

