### Interventions and electroacupuncture procedures

Local EA is given in group EA 1, while local with distal EA is given in group EA 2, additionally. The EA 1 group receives the same SOC therapy in combination with EA therapy at a total of two acupoints including *Zhong Wan* (CV12) and *Shang Wan* (CV13). The EA 2 group also receives the same SOC therapy in combination with EA therapy at a total of 14 acupoints including *Zhong Wan* (CV12), *Shang Wan* (CV13), *He Gu* (LI4), *Nei Guan* (PC6), *San Yin Jiao* (SP6), *Xuan Zhong* (GB39), *Zu San Li* (ST36), and *Shang Ju Xu* (ST37) (Fig. 1) [14, 16, 17]. Electric stimulation is applied with mixed frequencies (30 and 3 Hz). Each EA session lasts 15 min (STN-330 electronic stimulator, Stra Tek Co., Ltd., Gyeonggi-do, Korea). Both EA groups receive auricular acupuncture therapy at a total of five auricular acupoints, including Sympathetic, *Shen Men*, Abdomen, Pancreas gall, and Spleen, alternately at the right or left side, whenever EA is given. Both EA groups undergo one session of EA daily from day 1 until day 4, or until pain resolves.

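### EA 2 repeats EA 1's two abdominal points, so it cannot mask an abdominal location effect, and no comparison in the trial isolates distal EA

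*Protocol article*

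**What the plan says.** The protocol article describes the second EA arm in three places.

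- **Interventions and electroacupuncture procedures.** "Local EA is given in group EA 1, while local with distal EA is given in group EA 2, additionally". For EA 1: "The EA 1 group receives the same SOC therapy in combination with EA therapy at a total of two acupoints including" CV12 and CV13. For EA 2: "The EA 2 group also receives the same SOC therapy in combination with EA therapy at a total of 14 acupoints including" the same CV12 and CV13, followed by six named points on the limbs. In addition, "Both EA groups receive auricular acupuncture therapy at a total of five auricular acupoints". No auricular treatment is described for the control group.
- **Discussion.** "We set two different treatment groups, local and distal EA, to compare the effects according to acupoints". The reasoning is that the two abdominal points might act on abdominal pain because of where they are, so a further arm, called there the distal EA group, was introduced: "The treatment in the distal EA group is expected to mask the location effect in the abdomen". The Discussion then adds that "the comparison between the two EA groups will provide valuable information on the effect of distal acupuncture in patients with abdominal pain".
- **Abstract, Methods.** EA 2 is local EA with distal EA added, "while distal EA includes 12 peripheral acupoints". The list that follows has eight names and opens with the abdominal points CV12 and CV13.

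The Statistical analysis section plans a three-group comparison and a pooled EA-versus-control comparison. Post hoc comparisons, Bonferroni-corrected, follow only if the three-group test is significant.

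**The concern.** An arm can separate an effect of needling the abdomen from an effect of needling elsewhere only if it leaves the abdomen out. EA 2 does not. The reason given for the arm is therefore a property that the design lacks, and the Discussion's shorthand for the arms suggests a local-against-distal comparison that was not set up.

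What is at stake is the claim that the trial may make about acupoint location. The one comparison that bears on the distal points is EA 2 against EA 1. As the analysis is written, it may not be made at all if the three-group test is not significant, and it is imprecise when it is made.

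**Working it through.** **1. The plan's own sample size, as a reference.** Inputs from the section on planned number of subjects: SD 19 (test) and 25 (control), difference 20, 90% power, 5% level. The Statistical analysis section gives two-sided testing.

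n per arm = (1.960 + 1.282)² × (19² + 25²) / 20² = 10.51 × 986 / 400 = 25.9, so 26. The plan states 25, which gives 89% power. Dropout: 26 / 0.8 = 32.5, so 33, as stated. The size is reproduced to within one patient per arm, and this point does not depend on it.

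**2. Composition of the arms (Interventions section).**

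| Component | EA 1 | EA 2 | Control |
|---|---|---|---|
| CV12, CV13 (abdomen) | yes | yes | no |
| Distal points, 14 − 2 = 12 | no | yes | no |
| Five auricular points | yes | yes | none described |
| Standard of care | yes | yes | yes |

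The total of 14 is reached if the six named limb points are needled on both sides: 2 + 6 × 2 = 14. That is an inference from the count, because the acupoint figure is not shown. On the same count, the abstract's 12 fits the limb points alone, yet its list includes the two abdominal points. Its label, count and list do not agree with each other.

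**3. What each contrast estimates.** Let L be the effect of the two abdominal points, D the effect of adding the distal points, and A the auricular effect. If effects add:

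- EA 1 − control = L + A
- EA 2 − control = L + D + A
- EA 2 − EA 1 = D

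L is in both EA arms, so the second arm neither removes nor hides it. L appears only together with A, so D cannot be set against L. D is the gain from the distal points given that the abdominal and auricular points are already in use. It would equal the effect of distal EA alone only under strict additivity, which these three arms cannot test. EA 2 − EA 1 also changes the number of EA points from 2 to 14 (from 7 to 19 with the auricular points).

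**4. Precision of EA 2 − EA 1.** Assumption: SD 19, the plan's test-group value, in both EA arms.

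- SE with 25 per arm = 19 × √(2/25) = 5.374
- 95% half-width = 1.960 × 5.374 = 10.5 (normal), or 2.011 × 5.374 = 10.8 (t, 48 df)
- If all 33 per arm are analysed: SE = 19 × √(2/33) = 4.677; half-width = 1.960 × 4.677 = 9.2

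Power by the normal approximation, Φ(δ/SE − z), with 25 per arm:

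| True gap δ (VAS points) | α = 0.05 | α = 0.05/3 |
|---|---|---|
| 5 | 15% | 7% |
| 10 | 46% | 30% |
| 15 | 80% | 65% |
| 20 | 96% | 91% |

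The right-hand column assumes that Bonferroni is applied over the three pairwise comparisons. It does not include the preceding three-group test, whose chance of passing also depends on the control mean.

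**The case against.** The case on the other side has real weight.

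- **The arms are defined correctly where it counts.** The Interventions section and the abstract's opening description both say that EA 2 is local plus distal EA. This stands: the misdescription is in the Discussion and in the abstract's point list, and the definition of treatment in the Interventions section is not in doubt.
- **Local against local plus distal is an ordinary add-on design.** This also stands. A reader might infer that the second arm says nothing about distal points. The documents do not support that: EA 2 minus EA 1 is a valid randomised estimate of the add-on effect, and the Discussion names that comparison as the source of its distal information.
- **The protocol does not misread EA 2 against control.** A reader might infer from the masking sentence that a win for EA 2 over control will be presented as a distal effect. The article nowhere interprets that comparison in this way, so it is not a fault of the plan.
- **Nothing operative uses the masking idea.** The study aim, endpoints, sample size and tests do not refer to it. This stands, and it limits the consequence to what the trial may claim.
- **Low power for EA 2 against EA 1 is not an error, because the trial was sized for test against control.** Agreed. The precision figures show how little a null result on this contrast would say. They do not show a sample size mistake.
- **Reporting detail may sit in an analysis plan that is not shown.** This is fair for most reporting matters. Here, though, the article itself makes pairwise comparison conditional on the three-group test while promising information from one of those comparisons.

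None of this rescues the statement that EA 2 masks the abdominal location effect.

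**Conclusion.** The point holds as a fault of rationale and labelling, with one consequence for reporting. Because both EA arms contain CV12 and CV13, the masking claim and the local-against-distal comparison are not properties of this design. That conclusion follows from the listed components and needs no numerical assumption.

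The add-on contrast is valid but weak. With SD 19 in both arms and 25 evaluable patients per arm, its 95% CI extends about 10.5 to 11 VAS points either side, more than half of the 20 points for which the trial was sized. A finding of no difference between the EA arms would therefore leave a sizeable distal contribution open. A smaller SD, for instance after covariate adjustment, or more analysed patients would narrow this.

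A reader might go further and infer that the comparison of EA with control is compromised. It is not: that question and its sample size stand as planned.

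**What to change.** Change the text of the protocol and analysis plan as follows.

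1. Delete the Discussion sentence on masking the location effect.
2. Call the arms *local* and *local + distal* throughout.
3. Reconcile the acupoint list and count in the abstract with the Interventions section.
4. State what the contrasts estimate. Each EA arm against control estimates that arm's whole package, including the five auricular points. EA 2 minus EA 1 estimates the effect of adding the 12 distal points to local EA, with the number of points changing as well. No contrast isolates distal EA or compares it with local EA.
5. Report EA 2 minus EA 1 with its 95% CI whatever the three-group test shows.

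The cost is a few sentences and one extra interval. The downside is a narrower claim for the second arm. Treatment, randomisation and sample size do not change. The article describes the trial as still recruiting, so on that status the wording can be settled before results are interpreted.

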## Trial status

This trial is currently recruiting patients, and expected to be finished on 29 February 2020.

## Abbreviations

AP: Acute pancreatitis
EA: Electroacupuncture
IRB: Institutional Ethics Review Board
SOC: Standard-of-care
VAS: Visual Analog Scale
